### **6.2.7. Patient-reported treatment satisfaction**

- Participant's treatment satisfaction measured using the treatment satisfaction questionnaire for medication version 1.4 (TSQM v1.4) tool on a scale from 0 to 100, with a higher score indicating better satisfaction.

### **6.2.8. Patient-reported usability of the MERM device**

- Participants' experience using the MERM device measured by an 18-item questionnaire and the score transformed in to a scale from 0 to 100, with a higher score indicating better usability (Intervention arm only).

## **7. SIGNIFICANCE AND TRANSFORMING POTENTIAL**

This study will be the first in Ethiopia, and of the three in sub-Saharan Africa, to evaluate the effectiveness of pillbox-enabled SAT as a multicenter randomized controlled trial. The study will provide evidence of whether the pillbox-enabled SAT is non-inferior to the standard DOT for medication adherence and treatment outcomes. The study will assess whether digital adherence intervention is cost-effective, usable, and acceptable. The study targets TB patients living in Ethiopia - a high TB burden LMIC in Sub-Saharan Africa where alternative TB treatment strategies to in-person DOT do not exist.

If effective, this approach could substantially improve treatment adherence, increase sputum conversion, reduce patient-side costs due to daily DOT, and improve quality of life. It could also have a strong public health impact by reducing transmission of the disease to healthcare providers and the community at large as the approach can reduce patients' daily travels to healthcare facilities for in-person DOT. This approach will provide TB patients freedom and ownership of their treatment, which ultimately reduces mortality and morbidity thereby contributing significantly to the End TB Strategy. The findings will enable patients, healthcare providers, and policymakers to make informed decisions about the value of the intervention.

The study intends to use several clinical, biomedical, behavioral, and economic measurement tools to learn extensively about the desired outcomes of interest. The assessment of adherence using electronic, self-report, and biological specimens will provide credible and reliable justification of results. The diagnostic tools we plan to use are WHO-approved, and the questionnaires are valid and psychometrically sound for use in a local context. The study will collect original data from both patients and their TB care providers in local facilities, providing substantial evidence on the usability and acceptability of the intervention in real-world settings.

If the intervention arm is found non-inferior to DOT, the investigators will present the findings to the Ethiopian Federal Ministry of Health and work with the Bureau to scale up the intervention to larger healthcare facilities in Ethiopia. The investigators will also work with the World Health Organization and

donor agencies to see and discuss the scalability of the intervention to other high TB burden countries in Sub-Saharan Africa.

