# 1. PROTOCOL SUMMARY

## 1.1. Synopsis

Title: Electronic pillbox-enabled self-administered therapy versus standard directly observed therapy for tuberculosis medication adherence and treatment outcomes in Ethiopia: a multicenter randomized controlled trial (SELFTB trial)

Hypothesis: The use of a digital medication event reminder and monitor device-observed self-administered therapy provides non-inferior medication adherence and treatment outcomes for patients with TB compared with the standard in-person directly-observed therapy (DOT) in Ethiopia, one of the low-income countries with the highest burden of TB.

Objectives: Primary objectives:

1. To assess whether a digital medication event reminder monitor (MERM) device-observed self-administered therapy improves adherence in patients with TB compared with the standard DOT.
2. To assess whether MERM-observed self-administered therapy improves treatment outcomes in patients with TB compared with the standard DOT.

Secondary objectives:

3. To evaluate if MERM-observed therapy provides higher health-related quality-of-life (HRQoL) and lower catastrophic costs compared to the standard DOT
4. To evaluate the patient-reported usability and treatment satisfaction with MERM-observed self-administered TB therapy compared with the standard in-person DOT.

Outcome measures: Primary outcomes:

1. Level of adherence: Individual-level percentage adherence over the two-month intensive phase measured by adherence records compiled from MERM device vs. DOT records.
2. Sputum conversion: Participants with sputum smear converted following the standard two-month intensive phase treatment.

Secondary outcomes

3. Negative IsoScreen urine isoniazid test: Participants having at least one negative urine isoniazid test result (IsoScreen test, GFC Diagnostics Ltd, Bicester, England)

4. Adverse treatment outcome: Participants having at least one of the three events: treatment not completed; death; or loss to follow-up
5. Self-reported adherence: Participants who self-reported to have forgotten to take their medication
6. Health-related quality of life (HRQoL): The association between MERM-observed therapy and HRQoL, with the HRQoL measured and calculated for each participant by arm using the EuroQoL 5-dimension 5-level (EQ-5D-5L) score ranging from 0 to 1, with a higher score designating better HRQoL.
7. Catastrophic costs: Participants with overall TB treatment cost exceeding or equivalent to 20% of their income.

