#### **8.5.1.5. Sampling and sample size**

The sample size is calculated considering a 1-sided type I error of 2.5%, a power of 80%, 10% attrition rate, delta of 20%, non-inferiority margin, and a continuous outcome of percentage adherence over the two-month intensive phase, with a standard deviation of 36% and 79% of average adherence, assuming null hypothesis for both arms. The results yield a sample size of 57 in each arm for a total of 114 participants. We will do a  $\log_{10}$  transformation on the data, where a difference can be equivalently transformed into a ratio using a power ( $10^3$ ). The non-inferiority will be calculated as the log in the control minus the log in the intervention, which is equivalent to the log of the control divided by intervention.

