To compare the TSQM scores between study arms, independent t-tests will be done on log-transformed scores. Effects of the arms will be estimated using a geometric mean (GM) with geometric standard deviation (GSD) and mean ratios (MR) with 95% confidence intervals (CI). A general linear regression will be done on log-transformed TSQM scores to identify the effects of variables on participants' level of satisfaction. Effects will be measured using an adjusted mean ratio (AMR) with 95% CI. In all analyses, a 5% significance threshold will be used to determine statistical significance.

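### Two primary outcomes feed one non-inferiority verdict, but the protocol does not say whether both must succeed, and its 2.5% error and 80% power cover adherence only

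*Protocol*

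**What the plan says.** Sections 5.1.1 and 5.1.2 set two separate primary objectives. Sections 6.1.1 and 6.1.2 give each its own primary outcome: individual percentage adherence over the intensive phase, and smear conversion. The Synopsis words the second as "Sputum conversion: Participants with sputum smear converted following the standard two-month intensive phase treatment".

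The design figures are in Section 8.5.1.5: "considering a 1-sided type I error of 2.5%, a power of 80%, 10% attrition rate, delta of 20%, non-inferiority margin". The same sentence ties them to one outcome, "delta of 20%, non-inferiority margin, and a continuous outcome of percentage adherence over the two-month intensive phase", planned "with a standard deviation of 36% and 79% of average adherence, assuming null hypothesis for both arms". It yields 57 per arm. No margin, assumed rate or power is given for conversion.

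Section 9 compares adherence between arms by t-test on log-transformed percentages. The only test it names that would fit conversion is a chi-square test of association for categorical variables. It closes with "In all analyses, a 5% significance threshold will be used to determine statistical significance".

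Section 7 makes the practical consequence depend on one finding: "If the intervention arm is found non-inferior to DOT, the investigators will present the findings to the Ethiopian Federal Ministry of Health", followed by work on scale-up. That sentence names no outcome. The hypothesis in Section 4, and an earlier sentence in Section 7, join adherence and treatment outcomes in one statement.

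**The concern.** These statements do not fit together. Suppose adherence meets its margin and conversion does not. The hypothesis wording says the trial has not succeeded. The separate objectives, and a sample size built on adherence alone, leave room to say that it has. The scale-up sentence does not settle the matter, so the choice could be made after the results are known, and it could go against the clinical outcome.

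The operating characteristics depend on the same choice. A reader of Section 8.5.1.5 would take 2.5% and 80% as the trial's error rate and power. For the overall verdict, both figures hold together only if adherence alone decides, or if conversion has power close to 100%.

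**Working it through.** **Inputs from the protocol (8.5.1.5):** one-sided alpha 0.025, power 0.80, margin 20 points, SD 36, true difference read as 0, attrition 10%, 57 per arm. **Not in the protocol, so assumed:** the correlation between the two test statistics (0 to 0.8), and the conversion rate and margin. Adherence power is computed on the untransformed percentage scale, because that scale reproduces the stated sample size.

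**1. The plan's own figure.** n = 2(z₀.₉₇₅ + z₀.₈₀)² SD² / margin² = 2 × (1.96 + 0.8416)² × 36² / 20² = 50.9, so 51 evaluable per arm. 51 / 0.9 = 56.7, so 57. This matches. One-sided 5% would give 41 evaluable and 46 with attrition, which does not match. The whole one-sided 2.5% was therefore spent on adherence. Adherence power with 51 evaluable per arm is Φ(20 / (36√(2/51)) − 1.96) = 80.1%.

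**2. If both outcomes must succeed.** The one-sided error for the overall claim stays at or below 2.5%. Joint power cannot exceed the 80.1% for adherence. If conversion also had 80% power:

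| Correlation | Joint power |
|---|---|
| 0 (0.801 × 0.80) | 64.1% |
| 0.3 | 66.7% |
| 0.5 | 68.8% |
| 0.8 | 73.0% |

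The power for conversion is in fact unknown. As an illustration, take equal rates p in both arms, 51 per arm and margin m. Power is then Φ(m / √(2p(1−p)/51) − 1.96). Each cell shows conversion power, then joint power under independence:

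| Assumed p | m = 10 points | m = 15 points | m = 20 points |
|---|---|---|---|
| 85% | 29%, 23% | 56%, 45% | 81%, 65% |
| 90% | 39%, 31% | 71%, 57% | 92%, 74% |
| 95% | 64%, 51% | 94%, 75% | 99.6%, 80% |

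For 80% joint power with independent outcomes, each outcome needs √0.80 = 89.4% power. On the adherence side alone that is 67 evaluable, or 75 per arm.

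**3. If either outcome suffices, with conversion also tested at one-sided 2.5%.** The error is 0.05 − P(both reject under the null):

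| Correlation | One-sided error |
|---|---|
| Any (upper bound) | 5.0% |
| 0 (1 − 0.975²) | 4.94% |
| 0.3 | 4.76% |
| 0.5 | 4.54% |
| 0.8 | 3.90% |

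The stated error is 2.5%. A Bonferroni split to one-sided 1.25% would need 62 evaluable, or 69 per arm. At the planned 51 evaluable, adherence power would fall to 71.4%.

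**The case against.** The strongest reply is that rules for multiple outcomes are commonly left to a statistical analysis plan, which is not at hand. That stands as far as silence goes. The point rests instead on what the protocol does state: a flat 5% for all analyses, an error rate and power for one of two primaries, and an action that follows from an unnamed verdict. A later plan could add a rule, but Sections 7 and 8.5.1.5 would still read as they do.

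It can also be said that the scale-up sentence describes dissemination and is not a statistical decision rule. That is fair. It is nevertheless the only place where the protocol says what follows from a finding of non-inferiority.

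Three stronger readings are tempting, and the documents do not support them:

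- **That the trial runs at a false-positive rate near 4.5%.** This needs an either-outcome rule, which the hypothesis and Section 7 lean against. It also needs an assumed correlation of about 0.5, and a one-sided non-inferiority test on conversion that the protocol never describes.
- **That the protocol promises 80% power for the joint hypothesis.** Section 8.5.1.5 attaches the 80% to percentage adherence. The figure is correct for that outcome; the gap is that nothing is said about the joint claim.
- **That the unadjusted and adjusted mean ratios compete to decide adherence.** Section 9 gives the t-test to the comparison of arms and the general linear model to identifying effects of variables. Their stated purposes differ.

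**Conclusion.** The point holds in a limited form. As written, the protocol gives no determinate conclusion when only one primary outcome succeeds.

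The more natural reading is that both are needed, so the likelier consequence is lost power rather than excess error. The chance of supporting the hypothesis is capped at about 80% with the planned 51 evaluable per arm, and is 64% to 73% if conversion also had 80% power. How far below the cap it really lies cannot be computed, because no conversion rate or margin is given; the illustrated range is 23% to 80%.

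The excess error, up to 5% against 2.5%, is conditional on an either-outcome rule and a one-sided 2.5% test of conversion. The firmest gap underneath both is that no non-inferiority test for conversion is defined: a chi-square test of association cannot show non-inferiority. This is worth correcting before the data are analysed, and wording is enough to do it.

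**What to change.** - **Section 9:** state a fixed sequence. Test adherence first, by the t-test comparison of arms, at one-sided 2.5%. Test sputum conversion at one-sided 2.5% only if adherence passes. For conversion, compare a confidence interval for the difference between arms with a prespecified, justified non-inferiority margin, in place of the chi-square test of association. The second step cannot be carried out until that margin is written down.
- **Section 7:** state that the overall claim of non-inferiority to DOT requires both outcomes, and that success on adherence alone limits the claim to adherence.
- **Section 8.5.1.5:** state that the 80% is not the power for the joint hypothesis. Once the conversion margin is set, add the power for conversion with its assumed rate.

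The change needs no extra patients or data, and it keeps the full one-sided 2.5% and the 80% power for adherence, which a Bonferroni split would not. The price is that conversion cannot be claimed if adherence fails. The sequence makes the verdict determinate and holds the error rate; it does not raise joint power, which would need a larger sample.

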## 8. METHODS

### 8.1. Materials

The equipment for this study is an electronic pillbox, evriMed500 digital medication monitoring and reminder device manufactured by Wisepill Technologies, South Africa (Figure 5). It was developed with funding from the Bill & Melinda Gates Foundation and is currently in use in clinical trials and in clinical practice. The evriMED medication adherence device is an affordable and TB-appropriate digital medication adherence tool that has been tested extensively and is being used in India and China for TB patients. It costs less than 10 USD per patient based on conservative reuse assumptions, and it could easily be integrated into existing national health data systems. The device is TB-appropriate technology to permit customization of the container for Drug-susceptible-TB, MDR-TB and TB-HIV patients.

[figure not shown]

**Figure 5:** Electronic pillbox for adherence monitoring: components of the MERM module and its location in the container in which the medication blister cards are stored

The evriMED500 dispenser consists of two hardware components, namely the electronic module and the medication container. This modular design allows the electronic module to be reused and the container to be replaced if needed. The electronic module slots into the container so that the indicator LEDs are visible through the front of the container. A USB port can be accessed by opening the container. The electronic module has a USB port for downloading data and for configuration of the unit.

The container has three Indicator Lights/LEDs (green, yellow, and red). The green LED will flash once when the container is opened and again once when the container is closed; will quickly flash three times when the container is opened and closed quickly; will flash in sequence during the (daily) Medication Alarm; and will be on solid, while connected via USB to the computer. The Yellow LED is to refill medication and will flash with the Green LED at the time of the medication alarm. If the Medication Alarm is not enabled, only the yellow LED will flash. It will be on solid when the container is opened. The Red LED flash is for the battery, and it will flash with the Green LED at the time of the Medication Alarm. It will be on solid when the container is opened.

The device has a medication intake event in an electronic record that is created when a patient opens the device to take his or her medication. It consists of a date-and-time stamp. The dispenser provides an electronic heartbeat to a central management system whenever medication is taken, and this also indicates that the device was functioning during that period.

The alarm period is 30 minutes in length and consists of three-alarm cycles. The alarm cycles are 10 minutes each and made up of two parts. These alarms apply regardless of the type of reminder selected. The first five minutes of the alarm cycle is the active alarm. During the active alarm, the buzzer will sound, and the green LED will flash in the following sequence: short, short, long. The yellow LED will flash if the “Refill Alarm” is configured and the date is less than or equal to the current date. The second five minutes of the alarm cycle is the passive alarm. During the passive alarm, the buzzer will not sound, and the green LED will not flash. The yellow LED will continue to flash if the “Refill Alarm” is configured and the date less than or equal to today. Opening the container will cancel the active alarm if it is opened within four hours before the scheduled alarm or if it is opened during the alarm period.

The evriMED500 makes use of two AA batteries which should last for more than 12 months. Regarding storage capacity, it can store more than 12000 records/events. The evriMED PC Application is configured by the evriMED PC Application and it allows a direct connection to the evriMED device via a USB cable. Specification of the evriMED500 is summarized in table 2.

**Table 2:** Summary of evriMED500 specification

| Item                                                     | Specification                                                           |
|----------------------------------------------------------|-------------------------------------------------------------------------|
| Data Storage                                             | 12000 records                                                           |
| Battery Life (Alkaline)                                  | 12+ months                                                              |
| Power requirements                                       | Two AA batteries                                                        |
| Weight: Module + Standard Battery and Standard Container | 280g                                                                    |
| Dimension: Standard Container                            | 166.9 mm x 129 mm x 71.4 mm                                             |
| Dimension: Module                                        | 119.8 mm x 60.6 mm x 19.5 mm                                            |
| Material                                                 | Polypropylene Copolymer                                                 |
| Temperature range                                        | The Operating range is 0 to +50°C The storage temperature is 0 to +70°C |
| Relative Humidity                                        | 20% to 65% non-condensing                                               |
| Shock Resistance                                         | Withstands a one-meter drop onto a solid surface                        |
| Protection from Liquids and Dust                         | Dust and splash resistant                                               |
| Vibration                                                | 10 ~ 55Hz and amplitude 0.35mm                                          |
| Safety                                                   | IEC 60950-1:2013                                                        |

## 8.2. Trial design

The study will be a prospective, multicenter, randomized, controlled, non-inferiority, effectiveness-implementation hybrid type 2, two-arm trial. The study will not dictate diagnosis or treatment for TB; thus, it will not introduce or use new medications. Systematic and desk review methods will guide the study aimed at exploring the digital health ecosystem in Ethiopia.

## 8.3. Setting

Ethiopia is structurally divided into 11 autonomous administrative divisions. Addis Ababa, the capital, is among these administrative divisions and is the largest city of Ethiopia with the status of both a city and state. Addis Ababa is considered by some to be the capital of Africa, as it is a seat for the African Union headquarters and other international and regional organizations including the Africa Centers for Disease Control and Prevention. Administratively, Addis Ababa is divided into 10 sub-cities with distinct locations. As the city is crowded with population and housing, there is a high risk of TB transmission.

The national health and health-related indicator reports that in 2016, 2,290 bacteriologically confirmed TB cases were identified in the city, of which 1,811 (79.1%) completed their treatment and 1,526 (66.6%) were cured. For these reasons, Addis Ababa was chosen as the study setting.

#### 8.4. Site selection

In Addis Ababa, a total of 94 public health centers provide TB care and treatment services under the DOT program. This study stratifies the 94 health centers on the bases of the 10 sub-cities where they are located. From each stratified group, one health center with the largest TB client load will be selected, with a total of 10 health centers to be included. Health management information system (HMIS) quarterly data (April 01 - June 30, 2019) taken from the Addis Ababa Regional Health Bureau will be used for the purpose. This will give a representative sample of study sites and participants. A TB clinic in each center will serve as the study site and primary location for patient contact for that center. Table 3 lists out the 10 public health centers.

**Table 3:** Study sites

| S. No. | Name of Health Center       | Sub-city       | # PTB cases
bacteriologically
confirmed or referred
from other sites for
initiation of TB
treatment, April 01 -
June 30, 2019 |
|--------|-----------------------------|----------------|-------------------------------------------------------------------------------------------------------------------------------------------------|
| 1.     | Addis Raey Health Center    | Addis Ketema   | 41                                                                                                                                              |
| 2.     | Akaki Health Center         | Akaki kality   | 47                                                                                                                                              |
| 3.     | Kebena Health Center        | Arada          | 14                                                                                                                                              |
| 4.     | Goro Health Center          | Bole           | 31                                                                                                                                              |
| 5.     | Adisu Gebeya Health Center  | Gulele         | 22                                                                                                                                              |
| 6.     | Kazanchis Health Center     | Kirkos         | 19                                                                                                                                              |
| 7.     | Alem Bank Health Center     | Kolfe          | 38                                                                                                                                              |
| 8.     | Teklehaymanot Health Center | Lideta         | 22                                                                                                                                              |
| 9.     | Woreda 02 Health Center     | Nifasilk lafto | 53                                                                                                                                              |
| 10.    | Woreda 13 Health Center     | Yeka           | 35                                                                                                                                              |

The sub-cities selected should be willing and capable of participating in the study. If any health facility fails to do so, the study will consider the next facility with a large TB patient load. TB clinics in each of the study sites will be the primary sites for patient contact.

The study will be held as a collaborative undertaking between Addis Ababa University (Ethiopia) and Emory University (USA), and investigators from both institutions will take part in the study.

